## **Risks & Benefits**

This purpose of this study is to assess the safety, effectiveness including the clinical and technical performance and cost analysis of technology-assisted PCI versus standard PCI performed by a cardiologist in the context of a randomised controlled trial. The potential risk and benefits are listed below.

### 1.3.1 Potential Risks

Participants may be exposed to potential risks from participating in this study. Potential procedure and device related adverse events that may occur and/or require intervention are described below. The primary risks of the procedure are believed to be similar to the risks of participants undergoing procedures requiring PCI. Complications may occur at any time during the procedure. Potential risks of the PCI are:

- Injury to the hearts arteries including tearing and rupture
- Infection, bleeding and bruising at the catheter site
- Allergic reaction or kidney damage due to the dye or contrast used
- Blood clots that can lead to stroke or heart attack
- Bleeding into the abdomen

This study involves exposure to a small amount of radiation during the coronary angiogram which the participant would be receiving as standard care. Radiation may slightly elevate the risk for cancer. There is no increase in risk of exposure as a result of participating in this study.

Complications may occur at any time during the procedure. The study may involve unknown or unforeseen side effects or complications other than those mentioned above.

### 1.3.2 Potential Benefits

The CorPath System has shown clinical success in approximately 10,000 cases worldwide. The Precise Study demonstrated a 97.6% clinical success of all treated lesion (27) . A recent study showed that there is a reduction of unnecessary additional stents by 8.3% (28).

Radiation safety in the Interventional suite is also seen to be decreased with the use of the CorPath System by 20% for participants (29) and 95% to the primary operator (27).

There is limited real world evidence of the cost effectiveness of standard PCI versus technology assisted PCI. This study will help us to address this.

There may be other benefits that are unforeseen at this time.

### 1.3.3 Assessment of Potential Risk & Benefit

PCI is a standard care for Coronary Artery Disease (CAD). The complications of the procedure are explained to the participants prior to PCI and are similar in both arms of the study. The CorPath System is registered on the Australian Registry Therapeutic Goods (ARTG) for use in the remote delivery and manipulation of devices during percutaneous coronary and vascular procedures, including Guidewires, Rapid Exchange Catheters, Guide Catheters, Microcatheters, Neurovascular, Stent Retrievers, Embolization Coils and Coil Assist Stents. This study will use the device within indication.

The risk of collecting the data to compare two approved procedures has therefore been assessed as being low given that strict data protection is in place.

# Objectives & Endpoints

# Primary Objective

The primary objective of this study is assess the safety, effectiveness including the clinical and technical performance and cost analysis of technology-assisted PCI versus standard PCI performed by a cardiologist in a randomized clinical trial.

# Effectiveness Performance Measures

The following study measures will be evaluated in participants enrolled in this clinical trial. Parameters are participant-based or lesion-based.

### 2.2.1 Clinical Success

Defined as less than 30% residual stenosis (visual estimate) post PCI in the lesion(s) treated, without in-hospital MACE.

MACE is defined as cardiac death, clinically relevant MI after coronary revascularization (Q-wave or non-Q-wave myocardial infarction), or clinically driven target vessel revascularization (TVR) by PCI or CABG. Clinically relevant MI after coronary revascularization will be defined by the 4^th^ Universal Definition of PCI related MI. Events as classified by the Society for Cardiovascular Angiography and Interventions definition for periprocedural MI will also be recorded for additional analysis.

The 4th Universal Definition of PCI related MI defines:

- Participants with normal baseline cardiac biomarkers
  - Cardiac troponin (cTN) >5x the 99^th^ percentile of upper reference limit (URL)
- Participants with elevated baseline cardiac biomarkers
  - Rise in post procedure cTN by >20% and be at least >5x 99^th^ percentile of URL AND
  - At least one of the following
    - New ischaemic ECG changes
    - Development of new pathological Q waves
    - Imaging evidence of new loss of viable myocardium or new regional wall motion abnormality in a pattern consistent with an ischaemic aetiology
    - Angiographic findings consistent with a procedural flow limiting complication such as coronary dissection, occlusion of a major epicardial artery or a side branch occlusion/thrombus, disruption or collateral flow or distal embolisation

The Society for Cardiovascular Angiography and Interventions definition for periprocedural MI defines:

- Participants with normal baseline cardiac biomarkers
  - CK-MB >10x upper limit normal (ULN) or cTn (I or T) >70x ULN, or
  - CK-MB >5x ULN or cTn >35x ULN plus new Q-waves in >2 contiguous leads or LBBB
- Participants with elevated baseline cardiac biomarkers
  - Baseline biomarkers are stable or falling:
    - CK-MB >10x ULN or cTn (I or T) >70x ULN of **most recent pre-procedure level**, or
    - CK-MB >5x ULN or cTn >35x ULN of **most recent pre-procedure level** plus new Q-waves in >2 contiguous leads or LBBB
  - Baseline biomarkers have not been shown to be stable or falling: CK-MB (or cTn) rises by an absolute increment equal to those recommended above plus new ST-segment elevation or depression plus signs consistent with a clinically relevant MI, such as new onset or worsening heart failure or sustained hypotension.

## **Technical Success**

Defined as successful completion of the PCI absent *unplanned* conversion to manual operation of guidewire or balloon/stent catheter or inability to navigate vessel anatomy or poor guide catheter support.

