## **Other Measures/ Procedural Characteristics**

The objective of this study is to compare standard PCI with technology-assisted PCI to collect real-world data. When the PCI is being performed in conjunction with a diagnostic procedure, all efforts should be made to isolate the PCI procedural characteristics from the diagnostic procedure. At the end of the diagnostic procedure or alternatively to coincide with the PCI procedure time record the contrast, fluoroscopy time, DAP & AK at the end of the diagnostic procedure. When the PCI procedure is finished, record the values for these characteristics accumulated during the PCI procedure and not the diagnostic procedure. Procedures will be identified as staged (PCI only) or ad-hoc (LHC possible PCI). Any requirement to move from technology-assisted PCI to standard care will also be captured.

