### Standard PCI Technique

PCI will be performed as per the Institutional PCI procedure. Operators will be encouraged to raise the operating table as high as possible and use shuttering and collimation techniques to limit X ray exposures to the patient and staff.

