### Conversion to Manual Procedure Data Collection

The Investigator shall determine if it is necessary to convert to standard manual percutaneous techniques to complete the PCI. The Investigator should make this decision based on his/her medical assessment of the situation in accordance with the best interest of the participant. It is recommended that conversion to manual operation be performed at the discretion of the Investigator or if any of the following occur:

- The inability to navigate the guidewire or balloon/stent catheters using the CorPath GRX System as intended.
- Any clinical condition that requires rapid medical intervention.

The reason for conversion to manual should be reported by the operator and documented.

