# Data Management, Statistical Analysis and Record Keeping

## **Statistical Methods**

This is a double-arm, open-label, randomized controlled trial of the CorPath GRX System designed to evaluate the safety and effectiveness of the clinical and technical performance of the CorPath GRX System in the delivery and manipulation of coronary guidewires and stent/balloon catheters, and remote manipulation of guide catheters for use in PCI in comparison to standard of care. The analysis of data collected as part of the RCT will include, but may not be limited to, the Objectives and Measures outlined in Section 3.0 of this protocol. Continuous variables will be summarized using the number of observations, mean, standard deviation, median, min and max values. Categorical variables will be summarized with the number and percent in each category out of the number observed. Two-sided 95% confidence intervals may be calculated and two-sided p-values < 0.05 will be considered statistically significant.

The outcome of patient radiation exposure will be analysed using variance (ANOVA). As each participant may have multiple lesions, the outcome of clinical success at day 3 will be analysed using a two level multilevel models. Logit link will be used with a binomial distribution and restricted maximum likelihood (REML) will be used for estimation. Predictor variables in the models will include treatment group.

Technical success will analysed with Fisher’s exact test, comparing the proportion of participants with technical success between the two groups. Logistic regression will be used to compare technical success accounting for lesion complexity. For all other secondary outcomes, continuous outcomes will be measured using independent t-test (or non-parametric alternative depending on distributional assumptions), and categorical outcomes analysed by Fisher’s exact test. For outcomes measured repeatedly over time, multilevel models with an appropriate link functions will be used for analysis.

All statistical analyses will be performed using SAS software (version 9.4) or other widely accepted statistical or graphical software.

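### Technical success counts unplanned conversion to manual, which only the CorPath arm can suffer, yet it is tested between arms, so the comparison is biased against the device

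*Protocol*

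**What the plan says.** Section 2.3 (repeated in the protocol summary) gives one definition for the whole trial. It opens "Defined as successful completion of the PCI absent" and then lists what must be absent: unplanned "conversion to manual operation of guidewire or balloon/stent catheter or inability to navigate vessel anatomy or poor guide catheter support". There is no separate version for the manual arm.

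Section 8.1 fixes the analysis. Fisher's exact test is used, "comparing the proportion of participants with technical success between the two groups", and then "Logistic regression will be used to compare technical success accounting for lesion complexity". Two-sided p below 0.05 counts as significant.

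On the arms themselves, section 7.2.4 says of control that "PCI will be performed as per the Institutional PCI procedure", and section 5.1.1 treats conventional PCI as manual PCI. Conversion is described in one direction only. Section 2.6 says "Any requirement to move from technology-assisted PCI to standard care will also be captured". Section 7.2.6 says "The Investigator shall determine if it is necessary to convert to standard manual percutaneous techniques to complete the PCI", and one listed trigger is "The inability to navigate the guidewire or balloon/stent catheters using the CorPath GRX System as intended".

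**The concern.** A comparison of proportions between arms needs an outcome that each arm could fail in the same way. Here one failure mode exists only in the CorPath arm. Suppose a difficulty arises in both arms, is managed by hand, and ends with the same good result. In the CorPath arm it is a technical failure; in the control arm it can be a success. Adjusting for lesion complexity does not help, because the asymmetry lies in the outcome and not in the case mix. Conversion is also partly at the investigator's discretion, in a trial that section 8.1 calls open-label.

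Technical performance is part of the primary objective in section 2.1. A significant p-value against the device could therefore be read as a finding about relative performance when part or all of it comes from the definition.

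**Working it through.** **The plan's own figure.** The only power statement (section 8.1) concerns patient radiation. The difference is 0.20 × 1284 = 256.8 mGy. The standard error is √((180² + 142.83²)/150) = 18.8, so the difference is about 13.7 standard errors and power is effectively 100%. The stated figure of more than 99% reproduces, but it says nothing about technical success. The protocol gives no expected failure or conversion rate.

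**Inputs.** From the protocol: 150 per arm, 1:1 allocation, two-sided 5%, Fisher's exact test. Assumed, and varied because the protocol is silent:
- s: the rate of failures open to both arms (non-completion and, on one reading, navigation or guide support).
- c: the rate of unplanned conversion, CorPath arm only.

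**Built-in difference.** The control failure rate is s. The CorPath failure rate is 1 − (1 − s)(1 − c). The difference due to the definition alone is c(1 − s). With s = 5% and c = 5%, CorPath is 1 − 0.95 × 0.95 = 9.75%, which is 4.75 percentage points above control even though the arms are equal on every shared component.

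**Counts needed for significance.** With no control failures and k CorPath failures, the two-sided Fisher p is 2 × C(150,k)/C(300,k).
- k = 5: p = 0.060.
- k = 6 (4.0%): p = 2 × 0.01485 = 0.030.
- k = 10: p = 0.0017.

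With 2 control failures, 10 CorPath failures are needed (p = 0.035). With 5 control failures, 15 are needed (p = 0.035).

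**Chance of a significant result against CorPath.** This was computed by exact enumeration of both binomial counts, keeping tables with Fisher p < 0.05 and more failures in the CorPath arm:

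| Conversion rate c | s = 0 | s = 1% | s = 2% | s = 5% |
|---|---|---|---|---|
| 0 (component removed) | 0.0% | 0.1% | 0.6% | 1.2% |
| 1% | 0.4% | 2.2% | 3.0% | 3.0% |
| 2% | 8.2% | 9.6% | 8.5% | 6.3% |
| 3% | 29.6% | 22.7% | 17.5% | 11.4% |
| 5% | 76.6% | 55.3% | 43.0% | 27.3% |
| 10% | 99.8% | 96.5% | 91.6% | 76.0% |

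The first row shows what the same test does when the definition is common to both arms. Everything above it in the lower rows is produced by the robotic-only component.

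**Logistic model.** If the control arm has no failures, treatment predicts success perfectly in that arm (quasi-complete separation). The maximum-likelihood odds ratio for treatment then has no finite value. With at least one failure and one success in each arm, this particular problem does not arise.

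**The case against.** A reader might infer that the result is settled in advance, or that technical success is mainly a measure of conversion. The protocol supports neither. The definition starts from successful completion, which a manual PCI can fail, and its navigation and guide-support elements can be read as applying to both arms. Conversion is one of three listed failure modes and is given no extra weight, although section 7.2.6 makes robotic navigation failure a trigger for conversion, so the components overlap.

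Nor should zero control failures be taken for granted. The lesion classes in Appendix A carry success bands of 60–85% (type B) and under 60% (type C), and the only exclusion criterion is unsuitability for robotic PCI. At conversion rates of 2% or less a significant result is unlikely. The sign can also reverse: with assumed failure rates of 10% manual and 3% CorPath, Fisher's test significantly favours the device 63% of the time.

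It is also fair to say that an unplanned conversion is a real failure of the robotic technique and worth reporting, that clinical success is already planned as a between-arm outcome, and that handling of separation can be left to an analysis plan.

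These points limit the size of the problem and how certainly it will show. They do not remove it. The definition and the tests are both fixed in this protocol, and together they compare unlike things. That conversion is a genuine device failure is a reason to report it within the CorPath arm. It does not supply a control counterpart.

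**Conclusion.** The point stands as a structural bias. One component of technical success can occur only in the CorPath arm, no control-arm version is given, and section 8.1 tests the result between arms. The expected difference due to the definition is c(1 − s). For shared failure rates of 0 to 5%, the chance of a significant result against the device is about 6 to 10% at 2% conversion, 27 to 77% at 5% and 76 to 99.8% at 10%, against at most 1.2% without the component. These figures rest on assumed rates, on equal shared failure in both arms, and on 150 evaluable participants per arm. The missing logistic estimate is conditional on no control failures.

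This should be fixed, but it does not threaten the trial as a whole. Section 8.1 places technical success among the secondary outcomes, and the sample size rests on radiation exposure.

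**What to change.** 1. In section 2.3, state that conversion-based technical success is a measure of the CorPath arm. Report the proportion with an exact 95% confidence interval (for illustration, 144/150 = 96.0%, interval 91.5 to 98.5%) and relate it to lesion complexity within that arm.
2. In section 8.1, remove the between-arm Fisher and logistic tests of this outcome.
3. If a between-arm comparison is wanted, define an arm-neutral outcome, such as successful completion of the planned PCI by whatever technique, and analyse it by randomised arm. Setting out comparable failure modes for each arm is an alternative.

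The cost is a few sentences in sections 2.3 and 8.1. The need for manual input, the reasons for conversion, and whether manual steps were planned are already recorded (sections 7.2.3, 7.2.6 and 7.2.7). The arm-neutral outcome may need one further case report form item, since completion of the planned PCI is not itself listed in section 7.2.3. It would count a successful manual bail-out as a success, so it should be shown beside the conversion rate. It would also partly overlap clinical success. The sponsor gives up one between-arm p-value that could not be interpreted.

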## **Safety Measures**

Several safety-based measures will also be utilized to confirm the overall safety of procedures involving the CorPath GRX System and standard of care. These measures include:

### Major Adverse Cardiac Events (MACE)

MACE will be measured at each visit of the study.

### Serious Adverse Events

All Serious Adverse Events (SAEs) from the start of procedure until the end of the study will be summarized.

## **Cost Measures**

The cost of standard PCI versus technology-assisted PCI will be measured using equipment utilisation and post procedural length of stay until discharge. The costs of these two measurements will be compared and summarized.

## **Other Measures/ Procedural Characteristics**

The objective of this study is to compare standard PCI with technology-assisted PCI to collect real-world data. When the PCI is being performed in conjunction with a diagnostic procedure, all efforts should be made to isolate the PCI procedural characteristics from the diagnostic procedure. At the end of the diagnostic procedure or alternatively to coincide with the PCI procedure time record the contrast, fluoroscopy time, DAP & AK at the end of the diagnostic procedure. When the PCI procedure is finished, record the values for these characteristics accumulated during the PCI procedure and not the diagnostic procedure. Procedures will be identified as staged (PCI only) or ad-hoc (LHC possible PCI). Any requirement to move from technology-assisted PCI to standard care will also be captured.

### Overall Procedure Time Measure

Defined as the time measured from the insertion of the hemostasis sheath until the removal of the guide catheter

### PCI Procedure Time

Defined as the time measured from the insertion of the guide catheter until removal of the guide catheter.

### Wiring Time

Defined as time measured from advancement of coronary wire out of guide catheter until it crosses the lesion

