# Study Intervention Discontinuation and Participant Discontinuation/ Withdrawal

In the event that the participant is randomized but does not go ahead to have PCI or there is a requirement to move from technology-assisted PCI to manual PCI they will not be discontinued from the study and the remaining study procedures should be completed as indicated by the study protocol. Any discontinuation of the participant after the PCI is described in Section 6.1.

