### Data to be collected during the procedure

- Guidewire activation to guidewire retraction
- Fluoroscopy time
- Participant and staff radiation exposure (dose area product (DAP) and air kerma (AK))
- Lesion characteristics (eg tortuosity, calcification and bifurcation)
- Operator assessment of stent length
- Robotic assessment of stent length
- Contrast volume
- Procedure end time (Guide Catheter out)
- Equipment utilisation
- Pre and post PCI stenosis percentage
- Need for manual input (if required) and reason for this
- Number of times stent visualisation technique (eg stent boost or clearstent) used
- Use of robotic algorithms (techIQ) to assist lesion navigation
- Any adverse events
- Use of intracoronary physiology and/or intracoronary imaging
- Operator survey of task load

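### Wiring time has no value for a lesion that is never crossed and no rule for failed wires or conversion, so it can be read as timing only the wire that succeeds

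*Protocol*

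**What the plan says.** Section 2.6.3 of the protocol defines wiring time in one sentence: "Defined as time measured from advancement of coronary wire out of guide catheter until it crosses the lesion". It does not mention a second wire, a change from robotic to manual wiring, or a lesion that is not crossed.

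Section 7.2.6 names as one trigger for conversion to manual technique "The inability to navigate the guidewire or balloon/stent catheters using the CorPath GRX System as intended". Section 6.0 keeps such participants: if "there is a requirement to move from technology-assisted PCI to manual PCI they will not be discontinued from the study". A converted case can therefore supply a wiring time to the CorPath arm.

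The data list in Section 7.2.3 has one guidewire interval, "Guidewire activation to guidewire retraction", and also "Need for manual input (if required) and reason for this". It has no separate entry for the time of crossing, of conversion or of abandoning an attempt.

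Section 8.1 does not name wiring time. By default it falls under the remaining secondary outcomes, for which "continuous outcomes will be measured using independent t-test (or non-parametric alternative depending on distributional assumptions". The same section recognises that a participant may have more than one lesion.

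**The concern.** The measure is meant to show how well the guidewire is handled, yet its clock stops only on success. That raises two problems.

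- **Uncrossed lesions.** They have no stop event, so they have no value and leave the comparison. They are not missing at random, because they are the failures.
- **Failed attempts.** In the definition the pronoun refers back to the wire, so start and stop can be taken to belong to the same wire. A wire that is withdrawn and replaced then contributes nothing. If robotic wiring fails and a new wire is passed by hand, the CorPath arm is credited with the manual wire's time alone.

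Wire exchanges can occur in both arms, but only the CorPath arm has the additional route of robotic failure followed by conversion. At stake is whether a between-arm difference in wiring time reflects the whole effort of crossing or only its last, successful part. Two operators could also time the same case differently under the present wording. If the times are not noted in the catheter laboratory, a later analysis plan may be unable to recover them.

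**Working it through.** **The plan's own figures.** The protocol gives no figure for wiring time. Its one power statement concerns patient radiation. A 20% reduction from 1284 mGy is 256.8 mGy. The root-mean-square of the SDs 180 and 142.83 is 162.48. With 150 per arm the standardised difference is 256.8 / (162.48 × √(2/150)) = 13.69, so power above 99% is reproduced. Nothing below depends on it.

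**How each case is timed under the two readings of Section 2.6.3**

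| Case | Clock belongs to the crossing wire | Clock runs from first wire out to crossing |
| --- | --- | --- |
| First wire crosses | Full time | Full time |
| Wire fails, second wire crosses | Second wire only | Both attempts |
| Robotic wire fails, new wire passed by hand | Manual wire only | Both attempts |
| Robotic wiring fails, same wire advanced by hand | Full time | Full time |
| Never crossed | No value | No value |

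The last row holds on either reading. Only the second and third rows depend on which reading is taken.

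**Size of the difference between readings.** All inputs are assumptions:

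- f, g: share of CorPath and manual cases with a failed attempt that the crossing-wire reading omits
- F: mean minutes lost per such case, taken as equal in both arms
- S_R, S_M: mean time of the wire that finally crosses, in each arm

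Crossing wire only: difference = S_R - S_M.

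All attempts: difference = (S_R + f×F) - (S_M + g×F).

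First minus second: shift = -(f - g)×F.

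With g = 2%:

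| f | f - g | Shift at F = 3 min | Shift at F = 10 min |
| --- | --- | --- | --- |
| 0% | -0.02 | +0.06 | +0.20 |
| 2% | 0 | 0 | 0 |
| 5% | 0.03 | -0.09 | -0.30 |
| 10% | 0.08 | -0.24 | -0.80 |

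A negative shift makes CorPath look faster than a count of all attempts would. It is zero when the failure shares are equal and reverses when manual wiring fails more often.

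The formula covers lesions that were eventually crossed. For uncrossed lesions the documents give no number and no direction.

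**The case against.** The strongest reply is that the definition does not exclude anything. It does not say that the clock restarts for a second wire, and it can be read as running from the first wire out until the lesion is crossed. That is correct: this is an undefined rule, not a stated exclusion.

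A reader might infer that the robot is made to look faster wherever it fails. The documents do not support that, for three reasons.

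- The definition applies to both arms, and nothing in the protocol shows that wiring fails more often with CorPath. The conversion route makes this plausible, but Sections 4.1 and 4.2 admit only participants judged suitable for robotic PCI, which should hold failures down.
- Uncrossed lesions go missing; they are not scored as fast. Since a lesion that the robot cannot wire may still be attempted by hand, there is no ground for assuming more uncrossed lesions in the CorPath arm.
- One could calculate how far the CorPath mean alone is understated, as f×F/(b + f×F) with b the time of a successful pass. Assumed values then give 0.15/4.15 = 3.6% (f = 3%, F = 5, b = 4 min) up to 1.0/3.0 = 33% (f = 10%, F = 10, b = 2 min). That formula has no manual-arm term, so it does not measure bias in the comparison.

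Wiring failure is also visible elsewhere. Technical success (Section 2.3) requires completion "absent *unplanned* conversion to manual operation of guidewire or balloon/stent catheter or inability to navigate vessel anatomy". PCI procedure time, "Defined as the time measured from the insertion of the guide catheter until removal of the guide catheter", includes failed attempts. Section 8.1 already allows a non-parametric test, so the t-test is not fixed.

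These points limit the weight of the concern but do not remove it. Procedure time mixes wiring with every later step, and a success rate does not correct a time comparison. The clause in Section 8.1 deals with the shape of a distribution, not with times that do not exist because wiring failed. Analysis details may be left to an analysis plan, but what is timed and recorded is set here.

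**Conclusion.** The point holds as a gap in a stated definition. An uncrossed lesion has no wiring time on any reading. On one natural reading, failed wires, and robotic attempts followed by a new manual wire, also drop out. The data list in Section 7.2.3 does not name the times that would settle the matter later.

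A bias toward CorPath is possible but not shown. It needs f greater than g. Under the assumed values (g = 2%, F = 3 to 10 min) it reaches 0.09 to 0.30 min at f = 5% and 0.24 to 0.80 min at f = 10%, and it is nil at equal failure shares.

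Severity is minor. Wiring time is one of several procedural characteristics, does not appear among the measures in the trial summary, and does not drive the sample size.

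**What to change.** - **Section 2.6.3:** define wiring time per lesion, from the first exit of the first coronary wire directed at that lesion until that lesion is first crossed by any wire or method. State that exchanges and conversion count, and that arms are compared as randomised.
- **Section 7.2.3:** record the time of first wire exit, the time of crossing and, where they occur, the time of conversion or abandonment. Reconcile the existing guidewire interval with the definition.
- **Section 8.1:** name wiring time under the non-parametric option already allowed. Rank uncrossed lesions worst, or censor them at abandonment, and allow for several lesions in one participant. Worst rank is the safer default, because censoring treats an abandoned lesion as if it might have been crossed as readily as any other.

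The change concerns timing and analysis only; the decision to convert is untouched. The cost is a few extra time fields, one sentence of definition and one line of analysis. The result becomes a median or rank comparison (or a time-to-crossing comparison if censoring is used) rather than a difference in means, and CorPath wiring time may look less favourable.
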